This study has several aims. The first objective is to verify the efficacy of the FC intervention for relatives of people diagnosed with Suicidal Behavior disorders (SBD) in an RCT with a Spanish sample of participants from mental health services. The second objective is to analyze the feasibility and acceptance of FC-SBD in relatives of people with SBD. The third objective is to analyze whether the changes produced in the psychological variables in the relatives after the intervention are related to changes in the psychological variables of the patients. The fourth objective is to analyze whether improvements in emotional regulation, validation, control and empowerment, and family functioning predict reductions in burden, anxiety, and depression, and improvements in the quality of life of relatives. Fifth, we will analyze the opinions, preferences, and perceptions of the relatives in both treatment conditions.

We propose the following hypotheses: a) After the intervention, all the participants in the two treatment conditions, Family Connections (FC-SBD) or Treatment as usual optimized (TAU-O), will improve their level of burden, anxiety, depression, quality of life, validation, dominance, and empowerment, and critical incidents in the family environment will be reduced (self-harm, suicide attempts, arguments, etc.). However, the participants in the FC-SBD condition will improve more than those in the TAU-O condition; b) After the intervention, both interventions will have good acceptance by the participants, but the FC-SBD condition will have greater acceptance; c) The changes produced in the psychological variables in the relatives after the intervention will be related to changes in the psychological variables of the patients; and d) The improvement that may occur in the family members with regard to burden, anxiety, depression, and quality of life will be predicted by the improvements in emotional deregulation, validation skills, empowerment, and family functioning.

In this article, we present the study protocol.

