### Methods and design

#### Study design

This study is a superiority trial. The study design consists of a two-arm randomized controlled trial (RCT). On the one hand, there will be two conditions: Family Connections (FC-SBD) or Treatment as usual optimized (TAU-O), and family members will be randomized to one of the two groups. Family members will be randomized taking into account that if a patient has more than one family member attending the group, they will be randomized together to be included in the same condition. The effects of the treatment will be measured before starting the group, afterwards, and at the six-month follow-up in order to know whether the effects are maintained in the long term. Figure 1 shows the flow chart. This protocol will follow the CONSORT statement (Consolidated Standards of Reporting Trials, http://www.consort-statement.org) [30, 31] and the SPIRIT guidelines (Standard Protocol Items: Recommendations for Interventional Trials) [32, 33].

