### Data analyses

Regarding data analysis, the CONSORT guidelines [57] will be followed. First, participants' scores in the two conditions before receiving the intervention will be compared to check that there are no significant differences between them on the outcome measures and that they are, therefore, comparable after randomization. ANOVAs will be conducted for continuous variables and Chi-square tests for categorical variables. For outcome measures at post-treatment, we will study whether the assumption of homoscedasticity is met with Leven's test. If this assumption is met, repeated-measures MANOVAs and F-tests will be used to compare the two experimental conditions. If the homoscedasticity assumption is not met, the Brown-Forsythe test will be applied. F-tests for statistical significance will be followed by post hoc comparisons. In particular, Tukey will be used when the homoscedasticity assumption is met, and Games-Howell if the homoscedasticity assumption is not met. Appropriate analyses will also be carried out to calculate intervention effect sizes and confidence intervals. The intention-to-treat principle will be used when analyzing pre- and post-treatment data and at six-month follow-up, using mixed-effects models with full information and maximum likelihood estimation. This method has been recommended due to its flexibility in handling missing data [58]. To complement the MANOVA results and post hoc comparisons, effect sizes will be calculated using the standardized mean difference proposed by Cohen [59]. These effect sizes will be calculated to assess changes within and between groups, all based on a pooled standard deviation. Although per-protocol analyses (only analyses of data from participants who complete treatment) suffer from selection bias, they will also be conducted because they allow conclusions to be drawn about the maximum efficacy of the intervention in participants who are fully compliant with treatment. However, when the trial is over, the analytical methodology for controlled clinical trials will be reviewed before analyzing the data to select the most appropriate analytical procedures.

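### The post hoc tests named after the repeated-measures F-tests (Tukey, Games-Howell) are redundant on two arms and, in independent-groups form, too conservative if used on visits

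*Protocol article*

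**What the plan says.** The Data analyses section of the protocol article sets out a chain. It begins with a variance check: "For outcome measures at post-treatment, we will study whether the assumption of homoscedasticity is met with Leven's test". If variances are equal, "repeated-measures MANOVAs and F-tests will be used to compare the two experimental conditions". Then "F-tests for statistical significance will be followed by post hoc comparisons", and the choice of test depends on the variance check: "Tukey will be used when the homoscedasticity assumption is met, and Games-Howell if the homoscedasticity assumption is not met". The factor to which these comparisons apply (arm, visit, or arm-by-visit cell) is not named.

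The same section adds standardized effect sizes to complement the MANOVA and post hoc results: "These effect sizes will be calculated to assess changes within and between groups, all based on a pooled standard deviation". For data across visits it also names a second approach: "The intention-to-treat principle will be used when analyzing pre- and post-treatment data and at six-month follow-up", by mixed-effects models with maximum likelihood.

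Two stated questions involve comparing visits in the same relatives. Hypothesis (a) in the Background predicts improvement in both arms ("After the intervention, all the participants in the two treatment conditions"). The Study design section places measurements before the group, "afterwards, and at the six-month follow-up in order to know whether the effects are maintained in the long term".

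**The concern.** Each relative is measured at pretreatment, post-treatment and six months. In their usual form, Tukey and Games-Howell treat the means being compared as coming from different people. Levene's test, which selects between them here, is also a check on variances across independent groups. With only two arms, the F-test already settles the arm comparison, so the only factors with more than two levels are visit and the arm-by-visit cells. Those are the places where the means share the same people.

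If the tests are used there with an independent-groups error term, the covariance between visits is dropped. With a positive correlation the standard error is too large. Real improvement within an arm can then be missed, and so can a real loss of benefit between post-treatment and follow-up. The second matters because maintenance at six months is a stated aim and the article gives no criterion for it.

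**Working it through.** **Inputs.** From the Sample size section: 45 evaluable relatives per arm, effect size 0.60, two-sided alpha 0.05, power 0.80. From Study design: two arms, three visits. The article gives neither the between-visit correlation (ρ) nor a size of relapse. Both are assumptions here: ρ = 0.5 with range 0.3 to 0.7, and relapse of 0.4 SD with range 0.3 to 0.6 SD. SD is set to 1 at every visit, with equal correlation between visits.

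**1. The plan's own figure.** A two-sample t-test at d = 0.60 has power 0.795 with 44 per arm and 0.804 with 45 per arm. The stated 45 per arm (90 in total) reproduces.

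**2. Standard error of post-treatment versus follow-up within one arm.**
- True: √(2(1−ρ)/n). At ρ = 0.5 and n = 45 this is √(1/45) = 0.149.
- Independent-groups form: √(2/n) = √(2/45) = 0.211.
- True over assumed = √(1−ρ): 0.84, 0.71 and 0.55 at ρ = 0.3, 0.5 and 0.7.

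**3. Smallest observed difference that would be significant (ρ = 0.5).**
- Tukey over three visits, independent-groups error (132 df): 3.352/√45 = 0.500 SD, whatever ρ is.
- Paired contrast, Bonferroni for three pairs (44 df): 2.489 × 0.149 = 0.371 SD.
- Tukey on the repeated-measures error (88 df): 3.371 × √(0.5/45) = 0.355 SD.

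**4. Approximate power for a 0.4 SD relapse (ρ = 0.5).**
- Independent-error Tukey: Φ((0.4 − 0.500)/0.149) = Φ(−0.67) ≈ 0.25.
- Paired Bonferroni: Φ((0.4 − 0.371)/0.149) = Φ(0.19) ≈ 0.58.
- Repeated-measures Tukey: Φ((0.4 − 0.355)/0.149) = Φ(0.30) ≈ 0.62.

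**5. Simulation of the same contrast** (n = 45, relapse 0.4 SD; separate runs differ by about a percentage point):

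| ρ | Tukey, 3 visits, independent error | Games-Howell, 3 visits | Tukey, 6 cells, independent error | Paired, Bonferroni | Tukey, repeated-measures error |
|---|---|---|---|---|---|
| 0.3 | 29% | 29% | 13% | 42% | 46% |
| 0.5 | 26% | 26% | 9–10% | 58% | 62% |
| 0.7 | 21% | 21% | 5% | 83% | 86% |

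With no true change and ρ = 0.5, the independent-error contrast rejects in about 0.1 to 0.2% of trials. The figure is about 1.5 to 1.8% for the Bonferroni-corrected paired contrast and about 2% for Tukey on the repeated-measures error.

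**6. Other sizes of relapse (ρ = 0.5), independent-error Tukey over three visits against paired Bonferroni.** 0.3 SD: 10% against 33%. 0.5 SD: 51% against 81%. 0.6 SD: about 74% against 93%. Over six cells, Tukey detects 0.6 SD about 49% of the time.

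**The case against.** **The tests are not assigned to visits.** The chain opens with post-treatment outcomes, and the F-tests are described as comparing the two conditions. A reader might infer that Tukey and Games-Howell are prescribed for the three-visit data, but the text does not say so. It may be wording carried over from a design with more arms, which would be redundant and harmless. This stands. The visit reading is an inference from there being only two arms, supported by the within-group changes that the plan wants to assess. On either reading the sentence does no useful work.

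**Tukey is not invalid for repeated visits in itself.** It is a studentized-range adjustment, and the error term comes from the fitted model. On the repeated-measures error, with equal correlations, it matches or slightly exceeds the corrected paired contrast (62% against 58% at ρ = 0.5). This stands too. The fault lies with Games-Howell in its standard form and with Tukey on an independent-groups error. The article does not say which error term is meant, and selecting the test by Levene's test does not point to the repeated-measures one.

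**A mixed-effects model is already planned for all three visits, and methods will be reviewed before analysis.** The model can carry the within-relative correlation, and its covariance structure may properly sit in an analysis plan that is not shown. But the article keeps the MANOVA and post hoc results alongside it and does not say that visit contrasts come from the model. A later review leaves room for correction without making one.

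**A reader might infer that a real relapse would usually be reported as maintained.** The documents do not support that. Nothing in them equates a non-significant post hoc test with maintenance. Even on the unfavourable reading, three-visit Tukey misses a relapse more often than not only at about 0.4 SD or less. At 0.5 SD it is about even, and at 0.6 SD it detects roughly three in four.

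**Conclusion.** The point holds in limited form. The named post hoc tests add nothing on a two-level arm factor. If used on visits or arm-by-visit cells in independent-groups form, they discard the within-relative correlation and are too conservative. With 45 relatives and a 0.4 SD relapse, the loss of power against a Bonferroni-corrected paired contrast is about 13 percentage points at ρ = 0.3 (42 − 29), 32 at ρ = 0.5 (58 − 26) and 62 at ρ = 0.7 (83 − 21). These sizes rest on the assumed correlation and relapse, on equal variances and correlations across visits, and on the inferred use of the tests on visits.

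It would be wrong to conclude that the main efficacy result is at risk. The between-arm comparison, on which the sample size is based, is not affected. What is touched is the within-arm part of hypothesis (a) and the maintenance aim. For pre-to-post change the error works against the programme. It could favour the programme only if non-significance at follow-up were taken as maintenance. Severity is minor to moderate.

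**What to change.** In Data analyses, delete Tukey and Games-Howell as post hoc tests. State that all visit contrasts (pretreatment to post-treatment, pretreatment to follow-up, and post-treatment to follow-up, within each arm and as arm-by-visit differences) come from the mixed-effects model already planned, with a within-relative covariance and a Holm or Bonferroni correction over the visit pairs. State also that maintenance will be judged from the confidence interval of the between-arm difference at six months, not from a non-significant post-treatment versus follow-up test.

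The cost is a change of wording, with no new data and no new model. The one practical consequence is that relapse within an arm will be detected more often, so a claim of maintenance becomes somewhat harder to make.

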### Sample size

The sample size for this study was generated from effect sizes found in other studies with relatives of people with mental disorders. In the literature, we found a controlled study by Grenyer et al. [22] on a psychoeducational group intervention protocol for family members of people with borderline personality disorder. On the one hand, they found medium to large effect sizes for dyadic adjustment (d=0.78) and family empowerment (d=1.4); on the other hand, they found medium effect sizes for burden (d=0.45) at post-test and 12-month follow-up. The results of these effect sizes are consistent with other studies on psychological treatments for other mental disorders, such as a meta-analysis by Baruch, Pistrang and Barker [34] on psychological interventions for bipolar disorder (Burden, g = -.80). Based on the results of these studies, we expect an effect size of 0.60 because the design of this study consists of two experimental groups. For the calculation of the sample size, we used the G*Power 3.1 software [35], taking into account an alpha of 0.05 and a statistical power of 0.80 in a two-tailed t-test. We need a sample size of 90 participants (45 relatives per condition) to reach an effect size of 0.60 for burden. Finally, we considered possible sample loss during the treatment program. Based on studies of interventions for relatives of people with borderline personality disorder, we expect a 30% dropout rate [17, 23, 27, 36, 37]. Therefore, taking this outcome into account, our study requires a total sample size of 124 participants (62 participants per experimental condition).

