
### Interventions

#### Interventions with family members

##### Family Connections Protocol for Relatives of Patients with SBD (FC-SBD)

The intervention lasts three months and includes 12 sessions with a weekly two-hour group format.

The FC program [23] is divided into six modules:Module 1: Up-to-date information and research on suicide (Epidemiology, frequency, Risk factors, protective factors).Module 2: Psychoeducation on the development of suicide, explanatory theories, available treatments, comorbidity.Module 3: Emotional regulation skills, skills of acceptance, validation, approach, awareness, and to decrease emotional reactivity.Module 4: Skills to improve the quality of relationships in family interactions (letting go of guilt and anger, acceptance skills in relationships).Module 5: Communication skills and effective self-expression.Module 6: Problem management and making safe plans for crisis management.All the modules include practice exercises, video viewing, and homework assignments. In addition, throughout the program, with the aim of increasing social support, the FC-SBD program provides a forum where participants can stay in touch and share common problems and solutions.

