##### Treatment as Usual Optimized Protocol (TAU-O)

Family members in this condition will continue to receive their treatment as usual in their care center of reference. In addition, we will optimize the treatment based on the recommendations of the international guidelines for the treatment of suicide. There will be one three-hour session in group format with the following component:Module 1: Updated information and research on suicide (Epidemiology, frequency, Risk factors, protective factors). Psychoeducation on the development of Suicide, Explanatory theories. Available treatments, and comorbidity.

In both conditions, after each face-to-face session, the participant will be asked to review the contents covered during the session as homework (independently of the homework corresponding to the specific module being addressed). All interventions carried out with family members will be performed by clinical psychologists or general health psychologists with at least a Master's degree or a doctoral degree and previous training in the administration of the programs.

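### The per-protocol completer contrast cannot support a claim of maximum efficacy, because completion means 12 sessions in one arm and one in the other

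*Protocol article*

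**What the plan says.** The Data analyses section of the protocol article has two layers. The first is a randomised comparison: "The intention-to-treat principle will be used when analyzing pre- and post-treatment data and at six-month follow-up", fitted with mixed-effects models by maximum likelihood. The second is an additional completer analysis. The plan grants that "per-protocol analyses (only analyses of data from participants who complete treatment) suffer from selection bias", but keeps the analysis because "they allow conclusions to be drawn about the maximum efficacy of the intervention in participants who are fully compliant with treatment".

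What there is to complete differs sharply by arm. For FC-SBD: "The intervention lasts three months and includes 12 sessions with a weekly two-hour group format". For TAU-O, on top of continuing usual care: "There will be one three-hour session in group format with the following component".

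The Sample size section gives one attrition figure, "we expect a 30% dropout rate", which is not split by arm. The article does not say what counts as completing in either arm.

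**The concern.** The sentence admits a bias and then draws the conclusion that the bias rules out. If completers are a selected group, comparing them across arms does not show what the programme does for people who attend fully. It mixes any effect of attendance with differences between the people who remain.

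This design sharpens the usual caveat. An FC-SBD relative who would give up partway through three months is removed from the contrast. A TAU-O relative with the same tendency needed to attend only once and probably stays in. The plan's general remark about selection bias does not mention this asymmetry.

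At stake is a supplementary result that the plan allows to be stated as a conclusion about efficacy, when it is a non-randomised comparison whose error could be a noticeable fraction of the effect the trial is sized to detect.

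**Working it through.** **Inputs from the document.** FC-SBD: 12 × 2 h = 24 h. TAU-O: 1 × 3 h = 3 h. Expected dropout: 30% overall. Planned size: 62 per arm. Planning effect for burden: 0.60 SD, two-sided alpha 0.05, power 0.80.

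**The plan's own figure.** A two-sample t-test with these inputs needs 44.59, so 45 per arm and 90 in total, as stated; power at 45 per arm is 0.804. The completer claim itself rests on no stated number. The 0.60 serves below only as a yardstick.

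**Assumptions the document does not give.**
- Completion in FC-SBD is 70% (the 30% dropout applied to that arm).
- Completion in TAU-O is 90 to 100%, with 70% as the equal-completion case.
- The correlation *r* between the tendency to complete and improvement runs from -0.5 to 0.5 and is the same in both arms.
- The true effect is zero.

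**Model.** Tendency to complete and improvement are bivariate normal with unit SD. If a fraction *p* completes, the mean improvement of completers is shifted by *r* × φ(z)/*p*, where z is the normal cut-off that leaves *p* above it. The bias is the FC-SBD shift minus the TAU-O shift; a positive value favours FC-SBD.

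**Worked case, 70% against 95%.**
- *r* = 0.3: 0.149 - 0.033 = 0.116 SD.
- *r* = 0.5: 0.248 - 0.054 = 0.194 SD.

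**Bias in SD across the range:**

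| *r* | TAU-O 100% | TAU-O 95% | TAU-O 90% | TAU-O 70% |
|---|---|---|---|---|
| 0.1 | +0.050 | +0.039 | +0.030 | 0 |
| 0.3 | +0.149 | +0.116 | +0.091 | 0 |
| 0.5 | +0.248 | +0.194 | +0.151 | 0 |
| -0.1 | -0.050 | -0.039 | -0.030 | 0 |
| -0.3 | -0.149 | -0.116 | -0.091 | 0 |
| -0.5 | -0.248 | -0.194 | -0.151 | 0 |

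Equal completion alone does not remove the bias. With 70% in both arms but *r* = 0.3 in FC-SBD and 0 in TAU-O, it is 0.149 SD. Both completion and correlation must match for it to vanish.

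**Against the yardstick.** 0.116/0.60 = 19% and 0.194/0.60 = 32% of the planning effect.

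**False-positive rate.** With 62 × 0.70 ≈ 43 and 62 × 0.95 ≈ 58 completers, a nominal 5% two-sided t-test rejects in about 8.8% of trials at *r* = 0.3 and 15.9% at *r* = 0.5. The rates are the same for negative *r*, with most of the excess then pointing against FC-SBD. This treats relatives as independent.

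**The case against.** The strongest reply is that the plan has already disclosed the flaw and does not depend on this analysis. Intention-to-treat mixed models are planned for every time point, the per-protocol result is an addition, and the sentence itself names selection bias. What remains is one over-optimistic phrase. The definition of a completer may also stand in a fuller document that is not shown.

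Much of this stands. The randomised comparison is untouched, and the missing completer definition is not held against the plan here. What does not stand is that disclosure cures the conclusion. The text gives the completer result its own inferential role rather than that of a sensitivity check, and a fuller document would not make that inference valid.

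A reader might also infer that the completer estimate is biased towards FC-SBD. The document does not support that. It gives neither completion by arm nor any relation between persistence and outcome. If relatives who are coping well stop attending, or if those who persist are the more burdened and improve less, the bias runs the other way. With a single dropout figure and equal arms, a reader could also take completion as equal, and with equal correlations the bias is then zero. A tilt towards FC-SBD is plausible but not shown. The uncertainty does not rescue the claim: an estimate that may err in either direction is not a maximum.

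**Conclusion.** The point holds as a fault in what the plan says may be concluded. A contrast of completers of 12 sessions with completers of one is not protected by randomisation and does not estimate maximum efficacy.

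The size and sign of the bias are unknown. Under the assumptions above it lies between about -0.25 and +0.25 SD: 0.09 to 0.15 SD in absolute size for a correlation of 0.3, 0.15 to 0.25 SD for 0.5, and nil if completion and correlation are equal in both arms. These figures rest on assumed completion rates and correlations and illustrate scale; they are not predictions.

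The consequence is limited, because the intention-to-treat analysis is planned and unaffected. The correction is still worth making, since it changes what the trial may claim and costs almost nothing.

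**What to change.** In the Data analyses section:

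1. Delete the maximum-efficacy justification.
2. State that efficacy conclusions rest on the intention-to-treat mixed models.
3. Label the completer analysis a supportive sensitivity analysis, open to bias in either direction because completion demands differ by arm.

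These steps cost a sentence or two.

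If the effect of attending is wanted, add a complier-average causal effect estimate with randomisation as the instrument and all randomised relatives included. Define exposure as any FC-SBD attendance or as the number of FC-SBD sessions attended. Avoid a high session cut-off: if 70% met it, the estimate would be the intention-to-treat difference divided by 0.70, or 1.43 times that difference, even if the other 30% had gained from partial attendance. In a skills programme spread over 12 sessions such gains are likely enough to matter.

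This option costs attendance records, one extra model and a wider interval. It relies on the exclusion restriction, that assignment affects outcome only through attendance. Using the number of sessions also assumes a constant effect per session.

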**Methods:**

The study design consists of a two-arm randomized controlled trial with two conditions: FC-SBD or Treatment as usual optimized (TAU-O). Participants will be relatives of patients who meet DSM-5 criteria for SBD. The caregivers` primary outcome measures will be the BAS. Secondary outcomes will be DASS-21, FES, DERS, QoL. The patient’s primary outcome measures will be the frequency of critical incidents with the family member with SBD. Secondary measures will be the INQ, PHQ-9, OASIS. Participants will be assessed at pretreatment, post-treatment, and 6-month follow-up. The intention-to-treat principle will be used when analyzing the data.

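### Two unranked efficacy analyses, with the choice of procedure deferred to the end of the trial, leave the primary test unfixed and the 5% error rate unguaranteed

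*Protocol article*

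**What the plan says.** All of the following is in the protocol article.

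- **Primary outcome.** The abstract states that for caregivers the "primary outcome measures will be the BAS". Assessments are at pretreatment, post-treatment and six months; neither of the later two is named as decisive.
- **First analysis (Data analyses).** For post-treatment outcomes, if Levene's test is passed, "repeated-measures MANOVAs and F-tests will be used to compare the two experimental conditions". If it fails, a Brown-Forsythe test is used. Effect sizes are later described as complementing the MANOVA, which reads as if the MANOVA leads.
- **Second analysis (same section).** Intention-to-treat analysis of the pre, post and six-month data is done "using mixed-effects models with full information and maximum likelihood estimation". The abstract gives intention-to-treat as the principle for analysing the data.
- **Additional analysis.** Per-protocol analyses are also planned, with an acknowledgement that they are open to selection bias.
- **Closing sentence of the section.** "when the trial is over, the analytical methodology for controlled clinical trials will be reviewed before analyzing the data to select the most appropriate" procedures.
- **Planning test (Sample size).** The trial is sized "taking into account an alpha of 0.05 and a statistical power of 0.80 in a two-tailed t-test".

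**The concern.** The Study design section calls this a superiority trial, and the Sample size section sets alpha at 0.05. Both presuppose one test of burden, fixed in advance. The Data analyses section offers two candidates without ranking them, then makes everything before its last sentence provisional.

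The two candidates can disagree. A standard repeated-measures MANOVA drops people with a missing visit, whereas a likelihood-based mixed model keeps them. The article does not state the MANOVA's analysis set, so this is an inference from how the method usually runs. At the article's own 30% dropout, 124 × 0.30 = 37.2, so about 37 relatives could count in one analysis and not in the other.

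The time point adds a further choice. The BAS asks about the past six months, while FC-SBD lasts three, so a post-treatment score partly covers time before treatment. The post-treatment and six-month contrasts are not interchangeable.

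If the method or time point were settled with results in view, a significant finding could not be read as a prespecified superiority test at 5%.

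**Working it through.** **1. The plan's own figure.** Inputs from the Sample size section: d = 0.60, two-sided alpha 0.05, power 0.80, two-sample t-test.

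- Normal approximation: n per arm = 2(z₀.₉₇₅ + z₀.₈₀)²/d² = 2(1.960 + 0.842)²/0.36 = 43.6.
- Exact noncentral t: 44 per arm gives power 0.795; 45 per arm gives 0.804.

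So "We need a sample size of 90 participants (45 relatives per condition) to reach an effect size of 0.60 for burden" reproduces. This shows that alpha 0.05 was planned for a single test of burden, and that the planning test is neither of the two named efficacy analyses.

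**2. What the deferral can do to alpha.** Trials were simulated with no treatment effect. From the article: 62 per arm, three visits, 30% dropout. Assumed: equal within-person correlation of 0.3, 0.5 or 0.7; dropout at random; one third of dropouts still assessed at post-treatment; no clustering of relatives of the same patient. There were 8,000 runs per correlation, so the Monte Carlo standard error at 5% is √(0.05 × 0.95/8000) = 0.24 percentage points.

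Stand-ins for the plan's analyses:
- MANOVA: Hotelling group-by-time test on completers.
- Mixed model: baseline-adjusted post-treatment comparison in everyone with post-treatment data.
- Per-protocol: t-test at post-treatment in completers.
- Two more for the widest set: a pre-post F-test in completers and a baseline-adjusted six-month comparison.

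| Rule for choosing | r = 0.3 | r = 0.5 | r = 0.7 |
|---|---|---|---|
| One of the five tests, chosen without regard to outcomes | 5.2% | 4.7% | 4.7% |
| Better of MANOVA and mixed model, after seeing results | 8.8% | 8.0% | 8.1% |
| As above, with per-protocol added | 10.7% | 10.4% | 11.3% |
| Best of all five, including six months | 15.3% | 15.0% | 15.1% |

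Each test fixed on its own gave 4.6% to 5.1%. If the MANOVA is read as a pre-post F-test only, the better of it and the mixed model gave 8.3%, 7.7% and 7.2%.

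**3. Reference values.** Two independent tests at 5% give 1 − 0.95² = 9.75%, and three give 1 − 0.95³ = 14.3%. The second row lies below 9.75%, as expected for two positively related tests.

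**4. Leaving the time point open.** Adding a six-month contrast to the two analyses can only raise the second row, and three tests at 5% cannot exceed 3 × 5% = 15%. The simulation did not isolate that combination. The last row also contains the per-protocol and pre-post tests, so it is an outer figure.

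**The case against.** The strongest reply is that the closing sentence places the review before the data are analysed. Data collected are not results seen, and step 2 shows that a choice made without regard to outcomes keeps about 5%. A reader might infer from the deferral that the 5% rate is already lost; the text does not support that. This objection stands, and it limits the point to a missing safeguard.

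A reader might also count four rival analyses. That too goes beyond the text. Brown-Forsythe is a stated conditional branch, and per-protocol is already presented as additional and prone to bias. Two unranked analyses remain, and the mixed model is at least the one tied to intention-to-treat. Larger inflation figures from choosing among ANCOVA, change-score and post-score tests would not describe this plan, which names none of these.

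Nor do the documents say who makes the choice or whether that person sees data by arm. Therapists and participants will know the allocation, but that does not show that the people choosing the analysis will know outcomes or dropout by arm.

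Finally, this is a condensed article, and finalising a model before analysis is ordinary work for a statistical analysis plan. This carries less weight. The article is not merely silent: it states that procedures will be selected once the trial is over, and a plan that fixed the test earlier would contradict it. The Procedure section blinds outcome assessors and conceals the sequence from clinicians, but no sentence extends blinding to the choice of analysis.

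**Conclusion.** The point holds as a conditional one. The primary outcome is fixed as BAS, but the test that decides it is not, and the article expressly defers that choice without requiring it to be blind to outcomes by arm or dated before those outcomes are seen.

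The 5% error rate is therefore not guaranteed. It is kept if the choice ignores the outcome data. It becomes about 8% to 9% if the more favourable of the MANOVA and the mixed model is picked after results are seen, and more if the time point is also open. These are risks that the wording permits, not error rates shown to apply. They rest on the assumed correlations, random dropout, simplified stand-ins for the two models, and no allowance for relatives of the same patient being randomised together.

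**What to change.** In the Data analyses section:

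1. Delete the closing sentence that defers the choice of procedure.
2. Name one primary analysis: the mixed-effects model for BAS in all randomised relatives, with the between-arm contrast at one stated time point, two-sided alpha 0.05.
3. Label the repeated-measures MANOVA and F-tests, with the Brown-Forsythe branch, as supportive. Keep per-protocol as the additional analysis it already is.
4. Permit changes to the primary analysis only by a dated amendment made before anyone sees outcome data by arm.

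The Participants section describes the study as ongoing, so this should be done before outcomes are examined. The cost is wording only, plus the loss of freedom to change the method at the end.
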